# Effectiveness and cost-effectiveness of a transdiagnostic intervention targeting alcohol misuse and psychological distress for men in Ukraine: study protocol for a randomised controlled trial

**DOI:** 10.1186/s13063-025-09143-8

**Published:** 2025-10-09

**Keywords:** Conflict, Alcohol, Mental distress, Scalable interventions, Randomised controlled trial

## Abstract

**Background:**

Ukraine has experienced armed conflict since 2014, with significant escalation in 2022. Since then, an estimated 3.7 million people have been internally displaced. Alcohol misuse remains a substantial public health challenge in Ukraine, with high levels of psychological distress among the displaced population. The current study aims to evaluate the effectiveness and cost-effectiveness of a transdiagnostic intervention (CHANGE) to address alcohol misuse and psychological distress through problem-solving therapy and selected behavioural strategies for managing alcohol misuse. We hypothesize that CHANGE, together with enhanced usual care (EUC), will be more effective in increasing the percentage of days abstinent (PDA) than EUC alone.

**Methods:**

This study is a parallel-arm, single-blind, individually randomised controlled trial across Ukraine government-controlled territories. Following informed consent, we will recruit 500 adult war-affected men, randomised 1:1 to EUC and CHANGE, or EUC alone. Inclusion criteria include elevated levels of alcohol use (between 8 and 19, inclusive, on the Alcohol Use Disorder Identification Test); psychological distress (≥ 16 on the Kessler Psychological Distress Scale) and ability to speak Ukrainian or Russian. CHANGE will be delivered over 6 weeks by 14 community-based facilitators, with outcomes assessed at 3 months post-randomisation. The primary outcome for CHANGE is the PDA from alcohol at 3 months, measured using the Timeline Follow Back. Secondary outcomes include percentage days of heavy drinking, alcohol misuse, psychological distress (depression, anxiety, and posttraumatic stress disorder), functional disability, intimate partner violence perpetration and health economics indicators at 3 months. The primary analysis will follow an intention-to-treat approach. A mixed-methods process evaluation will examine facilitator competency, recruitment, retention/completion, appropriateness, dose received, fidelity and feasibility of delivery and acceptability.

**Discussion:**

CHANGE is the first intervention aiming to address alcohol misuse and psychological distress in an active conflict setting.

**Trial registration:**

ISRCTN14881856. Registered on 5th of July 2024.

**Supplementary Information:**

The online version contains supplementary material available at 10.1186/s13063-025-09143-8.

## Administrative information

Note: the numbers in curly brackets in this protocol refer to SPIRIT checklist item numbers. The order of the items has been modified to group similar items (see http://www.equator-network.org/reporting-guidelines/spirit-2013-statement-defining-standard-protocol-items-for-clinical-trials/).

Role of sponsor {5c}	The sponsor has had no role in the design or submission of this protocol. Furthermore, they will have no role in the collection, management, analysis, and interpretation of data.

## Introduction

### Background and rationale {6a}

The conflict between Russia and Ukraine began in 2014 and escalated into a full-scale invasion on February 24, 2022. Since 2022, approximately 3.7 million people have been internally displaced, 6.5 million Ukrainian refugees have been recorded globally and an estimated 14.6 million people are in need of humanitarian assistance [1].

The World Health Organisation (WHO) estimates that 9.6 million people in Ukraine are currently at risk of or living with mental health conditions [2]. The Russian invasion of 2014 [3, 4] and the 2022 escalation have caused significant psychological harm to the Ukrainian population [5]. A 2016 survey reported that 21% of respondents had post-traumatic stress disorder (PTSD) [3]. Another survey conducted in the same year found high prevalence rates of PTSD (32%), depression (22%), and anxiety (17%) amongst internally displaced persons in Ukraine [6]. Mental health worsened in Ukraine following the 2022 invasion, with the most notable increases being in anxiety, depression, and loneliness [7]. A nationwide study conducted in 2022 looking at trauma exposure due to war-related stressors as a result of the most recent invasion found that all participants had been exposed to at least one war-related stressor, with 26% experiencing PTSD and 15% suffering from complex PTSD [5].

Mental health conditions, particularly depression and anxiety, have a strong comorbidity with alcohol misuse [8]. Adversity, including lack of a supportive environment, demoralization, mental health symptoms and the normalization of alcohol misuse all contribute to high prevalence rates of alcohol use disorders (AUDs) in Ukraine [9, 10]. Over 10,000 deaths in Ukraine were related to alcohol consumption in 2019, with more than 80% of these deaths occurring among men [11]. Similarly, a WHO survey conducted over two weeks at the end of November in 2023 in Ukraine revealed that 77% of respondents were current drinkers, of whom almost half (49.2%) reported heavy episodic drinking over the last 12 months. Among those who engaged in heavy episodic drinking, 64% were men [12]. However, the report noted that 22% of respondents reported a decrease in alcohol consumption since the full-scale invasion, which can be partly attributed to government-imposed restrictions on alcohol sales during the initial phases of the conflict, which were revoked after 3 months. In comparison, 6% reported they had started drinking more, and 3% returned to drinking after a period of abstinence [12].

Responding to both AUDs and psychological distress can help improve outcomes for both conditions; however, interventions that are freely available and easy to scale up are lacking. Ukraine’s mental healthcare system is characterized by a high priority for specialized and/or institutionalized settings, is highly fragmented [13], and provides limited options for community-based mental health services [14]. Despite a significant demand for mental healthcare and support, an estimated 74% of internally displaced persons (IDPs) in Ukraine are not accessing mental health services [6]. Barriers to help-seeking include a preference for self-medication, cost of health care, mental health stigma, lack of information, healthcare providers’ poor understanding of mental healthcare and the perceived poor quality of services [6]. The accessibility of healthcare services has in general significantly deteriorated due to the escalation of war, and Ukrainians face major barriers to accessing care [15]. Further, there mental health stigma is common among individuals and healthcare providers [13, 16], particularly for individuals with AUDs [13]. Due to this large treatment gap for mental health disorders in Ukraine, there is an urgent need to evaluate effective low-intensity interventions delivered by non-specialists (task-sharing) available to meet current and future mental health needs [17].

In response to the large global health burden for mental disorders, the WHO developed Problem Management Plus (PM +), a brief, low-intensity community-based psychological intervention delivered by lay healthcare workers [18]. PM + consists of five sessions and was designed for adults experiencing symptoms of common mental disorders such as depression, anxiety, stress or grief, alongside self-identified practical problems. As a transdiagnostic intervention, PM + uses common principles across various mental disorders without being tailored to a specific diagnosis. Research has shown that PM + effectively reduces stress and promotes positive mental health outcomes [19, 20]. The CHANGE intervention was developed through a systematic intervention development process [21] is informed by PM + , and incorporates additional evidence-based strategies to address alcohol misuse, which were identified through a meta-review.

This paper presents the trial protocol to test the effectiveness and cost-effectiveness of ‘CHANGE’, among war-affected men in Ukraine. This trial is part of a broader five-year project aimed at addressing alcohol misuse and related mental health comorbidities (i.e. depression, anxiety and post-traumatic stress symptoms) in war-affected men in Uganda and Ukraine [22]. We previously published the protocol for the comparison trial evaluating the effectiveness and cost-effectiveness of CHANGE in Uganda [23].

### Objectives {7}

The objective of this study is to assess the effectiveness and cost-effectiveness of the CHANGE intervention. Our primary hypothesis is that the combination of the CHANGE intervention and enhanced usual care (EUC) will be more effective than EUC alone in increasing percentage of days abstinent (PDA) at the 3-month follow-up, which is our primary outcome. Secondary hypotheses are that CHANGE combined with EUC will outperform EUC alone in reducing psychological distress, symptoms of depression, anxiety and PTSD; levels of disability; and intimate partner violence at the 3-month follow-up assessment. We also hypothesize that CHANGE combined with EUC will be more cost-effective in terms of cost per DALY averted and/or QALY gained, and result in greater cost savings for the user and the provider compared to EUC alone.

### Trial design {8}

The current study uses a parallel-arm, superiority, single-blind and individually randomised controlled trial (RCT) design with equal allocation between the control and interventions arms. CHANGE will be fully delivered in a remote format (online or via telephone). A mixed-methods process evaluation will be carried out investigating competency of facilitators delivering the intervention, dose received, fidelity and feasibility of intervention delivery and acceptability of participants with regards to CHANGE. The economic evaluation will investigate the cost-effectiveness of CHANGE compared to EUC from a user and provider perspective.

## Methods: participants, interventions and outcomes

### Study setting {9}

The CHANGE intervention will be implemented in a remote format (online via a voice or video call with a facilitator) among war-affected Ukrainian men living across all the Ukraine government-controlled territories. There are currently an estimated 3.7 million IDPs in the government-controlled territories (of whom 41% are male) [24], as well as an estimated 1.2 million veterans returning from military service [25]. It was necessary to focus solely on Ukraine government-controlled territories to mitigate against potential physical and psychological risks for participants residing in territories controlled by the Russian military and Crimea. We decided to implement the intervention in a fully remote format following participant preferences in the feasibility trial. The feasibility trial was conducted between September 2023 and April 2024 in Kyiv and Dnipro, in person and online (unpublished data). In the feasibility trial, martial law and intensified military recruitment negatively impacted on the recruitment and willingness of men to attend in-person activities due to fears of conscription and being seen in public. Concerns about personal data collection amid ongoing military recruitment, the changing safety situation, and attending sessions in person, also affected participant retention in the face-to-face format. Consequently, for the effectiveness trial the decision was made to conduct the program exclusively in a remote format.

### Eligibility criteria {10}

Study participant inclusion criteria are Ukrainian adult men (age ≥ 18 years) residing in a territory controlled by the Ukrainian government with (i) a score between 8 and 19 (inclusive) on the Alcohol Use Disorder Identification Test (AUDIT) [26], indicating alcohol misuse; and (ii) a score equal to or greater than 16 on the Kessler Psychological Distress Scale (K10) [27], indicating high levels of psychological distress. Finally, participants must be able to speak Ukrainian and/or Russian spoken in Ukraine.

Exclusion criteria are (i) men with severe AUD (AUDIT score ≥ 20) or non-hazardous alcohol consumption (AUDIT < 8 [26]; (ii) men identified as being at imminent risk of suicide or other life-threatening risk (determined through three brief questions: ‘In the last month, have you had thoughts about suicide (or harming another person) or a suicide plan (or a plan to harm another person)?’; ‘Do you have ways to carry out this plan?’; and ‘Have you tried to kill yourself (or to kill or harm another person) in the past month?’); (iii) men who express high levels of homicidal ideation (determined by the person having thoughts, plans, ways to carry out the plan and/or experience in harming another person). These individuals will be offered a referral to a psychiatrist; (iv) men identified as having signs of severe mental disorders such as psychosis and/or severe cognitive impairment, assessed through a checklist of observable signs (e.g. not understanding questions, presenting confused speech, or limited communication skills); (v) men who have received other formalized brief psychological interventions (e.g. PM + , Common Elements Treatment Approach (CETA)) in the last year, as well as those who have received treatment for substance misuse (e.g. Alcoholics Anonymous, detoxification, replacement therapy programs) at any point in their lifetime; and (vi) men who are actively involved in military action and those who reside outside of Ukraine will also be excluded. Outcome assessors will carry out the screening procedures and will be trained on providing support for referral pathways to specialised care.

Whilst the current study focuses on men, if women with harmful alcohol use and elevated psychological distress approach the study, they will be offered the option to complete the consent procedures and screening. If eligible, they will be offered the outcome measures, the CHANGE intervention and EUC. However, their data will not be used in this trial and will be analysed separately.

Fourteen community-based providers, referred to as ‘facilitators’, have been recruited and trained to deliver CHANGE in Ukraine in a remote format. Inclusion criteria for the facilitators are (1) preferred experience working with men who are veterans, internally displaced persons (IDPs), and other population groups affected by the war, (2) preferred prior experience in the social sector or in the field of humanitarian response, (3) speak Ukrainian and (4) have stable access to internet. Recruited facilitators included: psychologists by training (*n* = 10), psychologists in training (*n* = 2), social workers (*n* = 1), providers without mental health background (*n* = 1) with relevant experience in psychosocial activities and/or community work. Facilitators are based in different regions across Ukraine including Kyiv (*n* = 4), Dnipro (*n* = 3), Lviv (*n* = 1), Ternopil (*n* = 1), Khmelnytskyi (*n* = 1), Vinnytsia (*n* = 1), Kharkiv (*n* = 1) and Poltava (*n* = 2). Lastly, facilitators work across different organizations including the National University of Kyiv-Mohyla Academy (NaUKMA) Mental Health Centre, NGOs, community-based organizations, governmental organizations, and private practice.

### Who will take informed consent? {26a}

Verbal informed consent will be documented digitally by the outcome assessors before the screening and baseline assessment. For this, participants will receive a participant information sheet and consent text via email or online messaging app in advance (depending on their preference). At the beginning of the consent procedure that takes place on the phone or online, the outcome assessor will verbally explain the purpose of the study and answer any questions the participant may have. Participants will provide oral consent to alleviate concerns about being identified for military recruitment, an issue that emerged during the feasibility trial. A similar, yet separate, consent process will be conducted prior to the qualitative interviews for the process evaluation.

### Additional consent provisions for collection and use of participant data and biological specimens {26b}

No biological specimens will be collected during this trial.

## Interventions

### Explanation for the choice of comparators {6b}

Participants in the control arm will be offered EUC in a remote format (online or via the telephone). The participant will be asked to choose to connect via an online platform or to a telephone connection, considering power cuts, personal preference or other technical issues. EUC consists of a consultation session with one of two trained EUC specialists, who will go through an electronic information pamphlet which outlines information on reducing alcohol intake and managing psychological distress, as well as information for participants on alternatively available psychological services they can individually access. EUC was deemed an ethical comparator in the context of war by the research team and ethics committees.

### Intervention description {11a}

In addition to being offered EUC as described above, participants randomised to the intervention arm will be offered six sessions of the CHANGE intervention in a remote format. Based on the feasibility trial, an additional booster session may be included that focuses on reviewing the previously taught strategies (without introducing new ones) that can be provided to participants with high stress levels, providing extra time to practice and internalize them. A convenient online platform for the call will be agreed upon with the participants. These can include, but are not limited to, Zoom, Google Meets, Skype, Telegram or Viber.

The CHANGE intervention is a brief, transdiagnostic psychological intervention, informed by PM + and enhanced through strategies based on empirical evidence, which aim to address alcohol misuse [22, 23]. The initial PM + intervention uses strategies including problem solving, stress management, behavioural activation and accessing social support to address common mental health problems [18]. To develop the CHANGE intervention targeting alcohol misuse, firstly a meta-review was conducted [28] to identify evidence-based strategies for the management of AUDs. After this a systematic intervention adaptation process followed to incorporate strategies into PM + that address alcohol misuse including enhancing motivation to change drinking behaviours. CHANGE is composed of three phases each which include individual weekly sessions of approximately 90 min each with the facilitators (Table 1).

**Table 1 Tab1:** Outline of the three phases and psychological strategies included in each phase of CHANGE

Phase I	Phase II	Phase III
• Engaging the client • Assessments • Review from the assessments • Information about the CHANGE intervention • Understanding adversity • Understanding alcohol use • Goal setting for drinking • Specifying a change plan	• Changing drinking behaviours • Managing stress • Managing emotions • Managing problems • Behaviour activation • Strengthening social support	• Relapse prevention • Ending the intervention • Optional booster session
Basic helping and motivational skills		

### Criteria for discontinuing or modifying allocated interventions {11b}

If clinical deterioration, an adverse event (AE) or a serious adverse event (SAE) is detected throughout the course of the trial by an outcome assessor or facilitator, it will be promptly reported to the research team, trial sponsor, ethics committees and Data Safety and Management Board (DSMB), see Sect. 22 for further details. Where an AE or SAE occurs, participants will be referred to specialist support if deemed necessary by the research director and research team using previously developed remote referral pathways. Clinical deterioration includes instances where a participant is intoxicated during multiple sessions, reports suicidal ideation, or homicidal ideation. Participants who report suicidal ideation will only be referred to specialist services or withdrawn from the trial if they are at imminent risk of suicide, which involves having a plan in place. Participants referred to specialist support during baseline outcome assessment or the CHANGE intervention sessions will be withdrawn from the trial but may continue to receive the remaining CHANGE sessions. If participants are referred to specialist support at the 3-month outcome assessment, they will not be withdrawn from the trial. All facilitators and outcome assessors have received training in safety protocols for remote service delivery and to ensure adherence to best practice.

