### Participant timeline {13}

Community-based recruitment will be carried out with the help of the implementing partner and NGO WordsHelp who will recruit within their networks and member base using digital flyers and dissemination of information on Facebook and Instagram pages. Furthermore, recruitment will be facilitated online using social media platforms including Facebook, Telegram, Instagram and others by making available a flyer (the advertisement of the trial with the contact details (online registration form or phone number), and through mass media activities. When participants get in touch with the research team, interested participants will be contacted via the telephone by the research assistants responsible for the initial contacting (phone operators). The phone operators will establish whether the participant has a good understanding of the study, collect additional information to see if the person can benefit from participation, check the technological means to participate (e.g. having a stable internet connection, owning a laptop tablet or phone), their platform of preference (e.g. Google Meets, Zoom, telephone) and a date and time to meet with the data collector for eligibility screening. After the initial contacting, the phone operators will send a digital copy of an information sheet and the text of consent form to participants via messaging app or email to read before the remote meeting with data collector.

Outcome assessors will meet the participant at the date, time and on the platform of preference previously established. Participants are given a short safety briefing, including an overview of potential safety risks, and instructions on what to do in high-risk situations (e.g. missile attacks or air raids during the session), and are given the opportunity to ask questions. Participants are asked to give verbal informed consent before the eligibility screening is conducted. Written consent is not requested given the security concerns of signing documents. If verbal consent is provided, the outcome assessors go through the screening tool, and sociodemographic questions with the participant taking note of their responses using ODK. If eligibility criteria are met, outcome assessors continue to the baseline assessment.

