Following the baseline assessment, an EUC specialist will join the call or set up a separate call with participant (on a separate day) to go through an electronic information pamphlet (detailing information on reducing alcohol intake and managing psychological distress as well as outlining ways of contacting alternative psychological services). The EUC specialist will also carry out the randomisation procedure, as detailed in the section below. Those randomised to the intervention arm will receive their first CHANGE session the week after (see Fig. 1).

Participants will be followed up at 3-months after baseline for the outcome assessment. Additional qualitative interviews will be carried out at 3 months follow-up using a purposive sampling strategy. Qualitative interviews will be carried out with all intervention facilitators ( *N* = 14), supervisors (*N* = 4), outcome assessors (*N* = 2) and phone operators (*N* = 2), in addition to family members of participants (*N* = 20), participants in the intervention arm (*N* = 20), participants in the control arm (*N* = 20) and as many participants who dropped out as possible (Fig. 2).

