## Assignment of interventions: allocations

### Sequence generation{16a}

Stata 16.0 statistical software (College Station, TX, USA) will be used to generate a randomisation sequence by an independent statistician who is not part of the trial team. Randomisation will be blocked of 4, 6 or 8 participants in a random order. Participants will be individually randomised 1:1 to both arms of the trial by the EUC specialist following baseline assessment [23].

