A critical incident register will be maintained during the study to record specific SAEs and AEs. An overview of the types of SAEs and AES can be found in Table 5. SAEs and AEs that are detected during any of the outcome assessments or intervention sessions will be disclosed immediately to the local research director and site PI who will become unmasked. For each individual event, a report will be written. Based on the type of event, the participant will be asked to give consent for further evaluation, assessment, and/or follow-up by a designated health professional (see Table 6). If the participant experiencing an AE or SAE was in the intervention arm of the trial, and once they are referred to further care their data will be excluded from the analysis. Nonetheless, if they are able to, they can receive further CHANGE sessions. The exception to this is referrals for intimate partner violence, whereby participants will be encouraged to access protection services, but will not be excluded from the analysis.

**Table 5 Tab5:** Expected and unexpected SAE and AEs (adapted from Van Der Boor et al., 2024 [23])

	Expected	Unexpected
SAE	Victimization (violence against the trial participant or nuclear family)	Death of the trial participant due to suicide
	IPV (violence against family members by participant, or violence against participant by family member)	Death of the trial participant due to other causes
	Suicide attempt	Hospital admission of trial participant due to a psychiatric problem
	Homicidal ideation	Planning and/or going through with the homicidal ideation
	Stigmatisation	Hospital admission of trial participant due to other causes (i.e. serious medical emergency)
	Serious lack of food / Critically unsatisfied basic needs	
AE	Clinical deterioration of the participant	
	Emotional distress caused by a trial procedure (either by the outcome assessment or the intervention delivery)

**Table 6 Tab6:** SAE referral according to intervention arm

SAE	Reported at outcome evaluation in both arms, referral to:	Reported by facilitator in the intervention arm only, referral to:
Hospital admission of participant due to serious medical emergency^a^	General physician (GP), family doctor	GP, family doctor
Hospital admission of participant due to a psychiatric problem	Independent psychiatrist, Psychiatrist in the hospital	Independent psychiatrist, Psychiatrist in the hospital

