When an SAE is related to stigma, a report will be written as described above, and an evaluation will be conducted by an independent healthcare provider to ensure quality and correct identification of these types of SAEs. Irrelevant of the cause, for events determined by the independent clinician to be SAEs, the person who became aware of the event (outcome assessor or facilitator) will then forward the SAE for further referral to the appropriate professional. The time from initial detection of a potential SAE by the research team (e.g. outcome assessors and facilitators), to the responsible team member (outcome assessor or facilitator) sending the SAE/AE report to the nominated health professional is two working days. Following these 2 days, if it classifies as an SAE, the responsible team member will inform the research director, who will prepare and submit the report to the site PI, who will send it to overall PI, DSMB and respective ethics committees within 5 working days of detection. All SAEs and AEs will be followed up until they have abated, or until a stable situation has been reached. AEs will not be reported to the DSMB but will be included in the annual ethics report.

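### A man flagged for referral at baseline can be randomised before the referral is decided and then leave the trial, and the sections disagree on whether that exit depends on his arm

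*Protocol article*

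**What the plan says.** All references are to the protocol article.

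- **Withdrawal, section {11b}.** "Participants referred to specialist support during baseline outcome assessment or the CHANGE intervention sessions will be withdrawn from the trial but may continue to receive". What such men may go on receiving is any CHANGE session still outstanding. No arm is specified. Men referred at the 3-month assessment are not withdrawn.
- **Who decides, section {11b}.** When an AE or SAE occurs, "participants will be referred to specialist support if deemed necessary by the research director and research team". Section {17a} lists the research director as unmasked.
- **Screening, section {13}.** "If eligibility criteria are met, outcome assessors continue to the baseline assessment". Under section {10}, imminent suicide risk, high homicidal ideation and signs of severe mental disorder are exclusions at this step.
- **Randomisation, sections {13} and {16a}.** The EUC contact is described thus: "Following the baseline assessment, an EUC specialist will join the call or set up a separate call with participant (on a separate day". At that contact, "The EUC specialist will also carry out the randomisation procedure". On the order of events, section {16a} has: "Participants will be individually randomised 1:1 to both arms of the trial by the EUC specialist following baseline assessment".
- **Envelope, sections {16b} and {16c}.** The unlocking steps are set out in detail. None depends on a pending safety or referral decision.
- **Analysis exclusion, section {22}.** This covers events found at any outcome assessment, and section {12} counts baseline as one. Data are excluded after referral "If the participant experiencing an AE or SAE was in the intervention arm of the trial". Referrals for intimate partner violence are exempt here; section {11b} has no such exemption.
- **Analysis principle, sections {20a} and {20c}.** The primary analysis follows intention to treat.

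**The concern.** Something known before allocation should either stop a man being randomised or have no bearing on whether he is analysed. The withdrawal sentence fits neither case. It treats a man referred at baseline as a participant with CHANGE sessions still to come, which is possible only if he has been allocated.

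If flagged men are randomised first and removed later, two things are at stake. The first is balance: a decision taken after the envelope is opened, by a group that includes an unmasked member, need not fall equally on both arms. The second is the analysis set: under section {22}, a flagged man allocated to CHANGE would be dropped, while a man with the same baseline finding allocated to EUC would be kept. That is an arm-dependent exclusion for a pre-randomisation characteristic.

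**Working it through.** **Step 1: the sequence, as the sections allow it.**

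1. Screening is passed and the baseline assessment begins ({13}).
2. A problem is disclosed during baseline. It goes at once to the research director and site investigator ({22}).
3. The EUC specialist joins the same call and unlocks the envelope, or calls on another day ({13}, {16b}).
4. The research director and team decide whether to refer ({11b}).

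No section puts step 4 before step 3. On the separate-day route the decision may well come first. On the same-call route it need not.

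**Step 2: what happens to a flagged man once randomised.**

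| Section | Allocated to CHANGE | Allocated to EUC |
|---|---|---|
| {11b} | withdrawn | withdrawn |
| {22} | data excluded (except partner-violence referrals) | no exclusion stated |
| {20a}, {20c} | analysed as randomised | analysed as randomised |

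The three rows cannot all be followed.

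**Step 3: is power the problem?** Inputs from section {14}: 55% v 68% (13 points), SD 37, alpha 0.05 (taken as two-sided), 90% power, 20% loss, 250 per arm.

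- The plan's own figure: n per arm = 2 × (1.960 + 1.282)² × 37² / 13² = 170.2, so 171. Dividing by 0.80 gives 214 per arm, 428 in total. The stated 500 is larger than these inputs need.
- With 250 × 0.80 = 200 evaluable per arm: 13 / (37 × √(2/200)) − 1.960 = 1.55, giving power of 94.0%.
- With a further 10% lost from both arms (180 each): 13 / (37 × √(2/180)) − 1.960 = 1.37, power 91.5%.
- With a further 10% lost from one arm only (200 and 180): 13 / (37 × √(1/200 + 1/180)) − 1.960 = 1.46, power 92.8%.

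Power is not the issue.

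**Step 4: bias, on assumed values.** Suppose a fraction w of the CHANGE arm is excluded, and these men have PDA lower by g points than the CHANGE men who remain. The CHANGE mean, and hence the arm difference, is then overstated by w × g if no EUC man is excluded.

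| w (assumed) | CHANGE men of 250 | g = 10 | g = 20 |
|---|---|---|---|
| 2% | 5 | 0.2 points | 0.4 points |
| 5% | 12.5 | 0.5 points | 1.0 points |
| 10% | 25 | 1.0 points | 2.0 points |

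The design difference is 13 points. If the same fraction with the same gap left both arms, the shift would cancel in the difference. Neither w nor g is in the document. The table also assumes that every such man is randomised before his referral is decided, so it is an upper case for each rate.

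**The case against.** The best defence is the plain wording: referral occurs during baseline and randomisation follows it, so a referred man is simply not randomised. On this reading the phrase about remaining sessions belongs to the second group in the sentence, men referred during CHANGE sessions, and the fault is loose drafting. Immediate disclosure to the research director supports a quick decision. An envelope hold is the kind of detail a condensed article may leave to a standard operating procedure.

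Part of this stands. A reader might infer that randomisation precedes referral as a matter of procedure; no section says so, and the text supports only that it can. A reader might also use section {22}, where the interval for "sending the SAE/AE report to the nominated health professional is two working days", as proof of a late decision. That interval limits the sending of the report, not the referral decision.

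A reader might further infer that Table 6, which lists referrals for victimisation, stigmatisation and unmet basic needs, acts as a hidden exclusion of war-affected men. That would require each such referral to count as specialist support under section {11b}, which is not stated. The table's column for events reported at outcome evaluation may also mean follow-up only.

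The defence does not remove the conflict in Step 2. That conflict is between stated rules, not a missing detail, and the same-call route lets it apply to baseline findings.

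**Conclusion.** The point holds as a gap that the wording permits, joined to a real contradiction between sections {11b}, {22} and {20a}/{20c}. A man flagged at baseline could be randomised and then leave, and whether his data are dropped could depend on his arm.

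The size is unknown because no baseline referral rate is given. Screening has already taken out imminent suicide risk and high homicidal ideation, so the number may be small. Under the assumed 2–10% exclusion from CHANGE alone and a gap of 10–20 points, the overstatement is 0.2 to 2.0 points against a design difference of 13. Power stays above 90% in every case examined. The matter should be corrected because the departure from intention to treat is avoidable, not because a large distortion has been shown.

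**What to change.** 1. For any man flagged at baseline, keep the envelope locked until the referral decision is made, using the separate-day EUC call that section {13} already allows. Give him the next envelope in sequence when he is cleared, so the order checks in section {16b} still work.
2. Record men who do not proceed as not randomised, rather than withdrawn.
3. Keep every man already randomised in the intention-to-treat analysis in his allocated arm, whatever his arm or referral. This also covers men enrolled since recruitment opened in September 2024, and it can be settled before unmasking.
4. Reconcile sections {10}, {11b}, {13} and {22} on what a baseline referral means for trial entry, including the partner-violence exemption. Which findings call for referral or withdrawal is a clinical rule for the sponsor and is not proposed here.

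The cost is a change to the operating procedure and protocol wording, which needs the ethics approvals in section {25}. Flagged men wait a short time before randomisation, and a few may be lost while waiting. Unflagged men are unaffected.
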